	**Study period**					
	**Enrolment**	**Allocation**	**Postallocation**			**Closeout**
**Time point**	t-1	t0	t1	t2	t3	t4
**Enrolment**						
Eligibility screen	x					
Informed consent	x					
**Allocation**		x				
**Interventions**						
REWRITALIZE			x			
TAU			x			
**Assessments**						
*Baseline characteristics*						
Age	x					
Sex	x					
Employment status	x					
Highest education	x					
Diagnoses	x					
Time since diagnosis	x					
Earlier use of mental health services	x					
Prior admissions (#)	x					
Antipsychotics	x					
Suicide attempt	x					
Alcohol and drug abuse	x					
*Outcome measures*						
Personal recovery QPR	x			x	x	
Connectedness TBS	x			x	x	
Self-efficacy SEPRS	x			x	x	
Functioning WSAS	x			x	x	
Quality of life MANSA	x			x	x	
Overall mentalising MentS	x			x	x	
Alexithymia TAS	x			x	x	
*Outcome measures (subset, exploratory)*						
Cognition SCIP-D	x			x		
Social cueing, TASIT 2A	x			x		
Balancing other-perspective VISPT	x			x		
Positive and negative symptoms PANSS-6	x			x		
Functioning GAF-F	x			x		
*Safety measures*						
Admissions	x					x
Deaths						x
Suicide attempt	x					x

*QPR* Questionnaire for the process of recovery; *TBS* Thwarted belongingness scale; *SEPRS* Self-efficacy for personal recovery scale; *WSAS* Work and Social Adjustment Scale; *MANSA* Manchester Short Assessment of Quality of life; *MentS* Mentalization scale; *TAS* Toronto Alexithymia Scale; *SCIP-D* Screen for cognitive impairment in psychiatry; *TASIT 2A* The awareness of social inference test; *VISPT* Visual perspective-taking task; *PANSS-6* Positive and Negative Syndrome Scale; *GAF-F* Global Assessment of Functioning Scale

Table 5 shows the participant timeline and an overview of the data collection in agreement with the standard protocol items for randomised clinical trials, recommendations for intervention trials (SPIRIT) [17]. Data are collected and stored using REDCap, an electronic data capture tool hosted at the Capital Region of Denmark. REDCap is a secure, web-based software platform designed to support data capture for research studies [41, 42].

#### Sample size and power calculations

The minimum sample size is calculated based on the ability to detect a minimal but clinically significant difference between the active intervention group and the control group in the primary personal recovery QPR measure. The minimal clinically significant difference between the study groups has been estimated to 4 points [53]. Based on trials in similar populations, we assume a standard deviation of 10 in the study population, which corresponds to an effect size of Cohen’s* d* = 0.4 [104, 114]. To achieve a statistical power of 90% at a significance level of 5%, a total of 266 participants must be included in this study to detect a difference: 133 in each group. Based on the needed participants, power calculations for secondary outcomes were calculated and are presented in Table 6. Because of the relatively high drop-out rate in the pilot study and similar studies [64, 110], we will plan for a sample size of 150 participants in the active group and 150 participants in the control group. This should hence allow for at least a 90% power of finding a minimally clinically significant difference in the primary measure, i.e., the QPR measure of personal recovery.

**Table 6 Tab6:** Power

**Outcome**		**Measure**	**Alpha**	**Mean diff**	**SD**	**Cohen’s *****d***	**Power**	***n***	**Mean diff source**	**SD source**
*Primary*			0,05							
	Personal recovery	QPR		4	10	0,40	0,9	266	[53]	[114]
*Secondary*										
	Connectedness	TBS	0,05	14	14	1	1	266	[60]	[60]
	Self-efficacy	SEPRS	0,05	x^a^	x	0,40	0,9	266		
	Functioning	WSAS	0,05	5	7	0,71	1	266	[69]	[69]
	Quality of life	MANSA	0,05	4	11	0,36	0,83	266	[11]	[11]
	Overall mentalising	MentS	0,05	8	12	0,66	1	266	[29]	[29]
	Alexithymia	TAS	0,05	7	11	0,63	1	266	[66]	[47]

See Table 5 and the assessment tool section for outcome measure abbreviations

^a^Power estimates for measures for which no relevant mean difference was identified are based on a moderate to small effect size of Cohen’s* d*=0.4

For the pilot RCT no calculation of sample size has been made as the primary aim for a pilot RCT is to explore design uncertainties before proceeding to a future RCT [35], here feasibility of chosen measures.

#### Data analyses

The main outcome measure is personal recovery measured by QPR. To test the research hypothesis, the differences at follow-up between the active intervention group and the control group will be analysed using independent-samples t-test⁠. Effect sizes to judge clinical relevance will be estimated by Cohen’s d [19]. All variables are continuous. Secondary and exploratory measures will be tested by the same means. The significance level is set to 0.05 for all measures. If there, despite randomisation, are differences in any baseline measure between active and control groups, these differences will be adjusted for in the comparison between active and control groups using general linear models.

Data analyses will be based on the intention-to-treat principle. Data from all participants will thus be included in the analyses. In accordance with the principle, missing data from the follow-up will be imputed using multiple imputations by means of Markov Chain Monte Carlo methods in Stata. All co-variates of supposed prognostic significance will be used to impute a distribution of missing data. A prerequisite for multiple imputation is that data are missing at random. This will be examined by various means, e.g. by comparing prognostic baseline characteristics between the participants for whom follow-up data are missing and the participants for whom follow-up data have been collected.

As a supplementary analysis, the differences at follow-up between the active and control groups will be analysed including only observed data, i.e. data for whom follow-up data have been collected. A detailed statistical analysis plan will be prepared and uploaded to clinicaltrials.gov before initiating analyses.

For the pilot study mean, standard deviation, within and between group differences on the outcome measures will be calculated.

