The current intervention, REWRITALIZE, is a creative writing group intervention that is conducted by a professional author and focuses on the text as aesthetic form (see Intervention). Participants are instructed to respect the narrative distance, i.e., the distance between the narrated self and the self who narrates [38]⁠ and discuss the text rather than the person who wrote it. The protective distance between text and personal experiences is meant to establish a safe space in which participants can engage with artistic work on their own terms and express themselves spontaneously in both writing and reflective discussions about others’ art works. This is expected to allow participants to put into words difficult feelings or experiences, to practice mentalisation in reflective sessions, i.e., to reflect on their own and others’ mental states, relate to a plurality of perspectives and integrate others’ perspective into their own outlook [28, 46, 110], and to promote their self-efficacy ⁠[8, 9, 112]. Together this may reduce self-stigmatisation and illness identity, stimulate participatory meaning-making, enhance connectedness between the participants and inspire renegotiation of identity into a more positive self-conception, thus contributing to personal recovery [30, 43, 55, 57–59, 65, 67, 81, 91, 94, 98, 110, 113, 118, 119, 117]. Following studies in non-clinical populations pointing to reading and writing literature having possible impacts on social cognitive factors, it will be valuable to explore if the characteristics of the REWRITALIZE creative writing group intervention may also contribute to clinical recovery, i.e. cognitive and psychosocial functioning and symptom reduction.

The present study is part of a larger research program that has developed recovery-oriented, manualised, participatory arts groups, including REWRITALIZE with creative writing as artistic format [16]. The four phased design of this research program (Fig. 1) is based on recommendations from an international group of leading artist, arts researchers, and healthcare researchers, promoting complex interventions in healthcare treatment [36, 101, 102].

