### Participants

Participants in the RCT will be included in the study if they are over 18 and diagnosed with a severe mental illness, i.e., schizophrenia, schizotypal, delusional, and other non-mood psychotic disorders, bipolar disorder, severe depression, posttraumatic stress disorder, or borderline personality disorder (F2, F31, F32.2, F32.3, F33.2, F33.3, F43.1, F60.3). Forensic psychiatric patients will be excluded. In all, 30–34 groups, 15–17 active groups and 15–17 control groups, will be carried out with 8–10 participants in each group. Although power calculations (see below: Sample size and power calculations) set the minimum sample size to 266 and the RCT intention-to-treat principle reduces the threat of drop-out for power, we will aim to include 300 participants. Considering the relatively high drop-out rate in similar interventions [64, 110], the enhanced inclusion enables us to aim for a higher number of real, as opposed to imputed, follow-up data, and to minimise the risk to end up with low power if participants were to retract their informed consent.

Participants in the pilot RCT will be included in the study if they are between 18 and 35 and fulfil the criteria for a schizophrenia spectrum disorder (F20, F21) according to the Present State Examination [87, 115].

Participants will be recruited from outpatient clinics’ OPUS programs (early intervention program for first episode psychosis) and F-ACT (Flexible Assertive Community Treatment) at Mental Health Centres in Regions Capital and Zealand in Denmark [40, 75, 109].

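### The primary t-test, its linear-model fallback and the sample size treat active-arm participants as independent although they are treated in shared writing groups; if outcomes correlate within groups, the type I error exceeds 5%

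*Protocol article*

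**What the plan says.** All references are to the protocol article.

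- **Primary test (Data analyses).** "the differences at follow-up between the active intervention group and the control group will be analysed using independent-samples t-test". Secondary and exploratory measures follow the same method, and "The significance level is set to 0.05 for all measures".
- **Fallback (Data analyses).** If the arms differ on a baseline measure, "these differences will be adjusted for in the comparison between active and control groups using general linear models". No writing-group term is named.
- **Sample size (Sample size and power calculations).** "The minimal clinically significant difference between the study groups has been estimated to 4 points", "we assume a standard deviation of 10 in the study population", and "To achieve a statistical power of 90% at a significance level of 5%, a total of 266 participants must be included in this study", that is 133 per arm. The target is raised to 150 per arm because of expected drop-out, and this is said to secure at least 90% power.
- **Delivery (Participants; Intervention).** "15–17 active groups and 15–17 control groups, will be carried out with 8–10 participants in each group". The intervention is 15 three-hour sessions, led by an author and a co-conductor, in which participants discuss each other's texts.
- **Allocation (Assignment of interventions; RCT design).** Individuals are randomised 1:1, stratified by site. Controls are invited to a writing group only after their last assessment.

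The article mentions no ICC, design effect, group-level random effect or cluster-robust standard error.

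**The concern.** An independent-samples t-test and an ordinary linear model both require independent observations. Here 8–10 active-arm participants share the same peers, the same conductors and the same 15 sessions. The intended mechanism also runs through the group: the Background expects the intervention to "enhance connectedness between the participants and inspire renegotiation of identity", and connectedness is itself a secondary outcome. The Fidelity section plans checks across centres and conductor pairs, so it allows that delivery may vary. Positive within-group correlation is therefore likely in the active arm. Controls have no corresponding grouping when outcomes are measured. The design is partially nested.

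At stake are the p-value and confidence interval of the primary QPR comparison, and those of every full-sample secondary and exploratory comparison. The Discussion intends a positive result to support offering the intervention across Denmark. An analysis that ignores writing group does not count variation between groups as part of the uncertainty in that result.

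**Working it through.** **Inputs from the article.** QPR difference 4, SD 10, alpha 0.05, power 90%, 133 per arm (minimum) and 150 per arm (planned), group size m = 8–10.

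**Assumption.** ICC 0.01–0.10 within writing groups in the active arm. The article gives no value.

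**Step 1: reproduce the stated 266.** A two-sided t-test on independent observations with d = 4/10 = 0.4 needs 133 per arm (power 0.901), 266 in total. A one-sided test would need only about 108 per arm. The figure is therefore a two-sided calculation with no allowance for grouping.

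**Step 2: standard error with clustering in one arm.** With n per arm and equal total variance in both arms:

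- design effect in the active arm: DE = 1 + (m − 1) × ICC
- true variance of the arm difference: SD² × (DE/n + 1/n)
- variance the t-test assumes: SD² × 2/n
- ratio of true to assumed standard error: r = √[(DE + 1)/2]
- actual type I error: 2 × [1 − Φ(1.96/r)]

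Example, ICC 0.05 and m = 10: DE = 1 + 9 × 0.05 = 1.45; r = √(2.45/2) = 1.107; 1.96/1.107 = 1.77; type I error 7.7%.

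**Step 3: power of an analysis that allows for groups, at 150 per arm.** SE = 10 × √[(DE + 1)/150]; power = Φ(4/SE − 1.96). Same example: SE = 10 × √(2.45/150) = 1.278; 4/1.278 − 1.96 = 1.17; power 88%. The per-arm n for 90% power is (1.960 + 1.282)² × 100 × (DE + 1)/16.

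| ICC (assumed) | r | Type I error of planned t-test | Power at 150 per arm, normal approximation | Same, Satterthwaite df | n per arm for 90% (normal approximation) |
|---|---|---|---|---|---|
| 0 | 1.00 | 5.0% | 93% | 93% | 132 |
| 0.01 | 1.02 | 5.4–5.5% | 92–93% | 91–92% | 136–138 |
| 0.02 | 1.03–1.04 | 5.8–6.1% | 91–92% | 90–91% | 141–144 |
| 0.05 | 1.08–1.11 | 7.1–7.7% | 88–89% | 86–88% | 155–161 |
| 0.10 | 1.16–1.20 | 9.2–10.4% | 82–85% | 80–83% | 178–191 |

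Ranges run over m = 8 to 10. All power figures are before drop-out. At m = 8, 150 participants would fill 150/8 = 18.75 groups, more than the stated maximum of 17.

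**Step 4: simulation of the type I error** (20,000 runs per setting). For 17 groups of 8 and 15 groups of 10 respectively: 5.0% and 5.0% at ICC 0; 7.1% and 7.7% at 0.05; 9.1% and 10.3% at 0.10. This agrees with the formula.

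**Step 5: what would shrink the inflation** (both fractions are assumptions).

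- *Drop-out from the groups.* If 30% of the active arm had negligible exposure but stayed in the intention-to-treat analysis, a pair in the same group would both be exposed with probability 0.7² = 0.49, so DE = 1 + (m − 1) × 0.49 × ICC. The type I error becomes 6.0–6.3% at ICC 0.05 and 7.0–7.6% at 0.10.
- *Site-level correlation.* Suppose 0.02 of a within-group ICC of 0.05 is due to site. Stratification balances that part across arms, but the t-test still counts it as noise. The ratio of true to assumed variance is (0.03m + 0.95 + 0.98)/2, which is 1.085 at m = 8 and 1.115 at m = 10. The type I error is 6.0–6.3%.

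**The case against.** **No ICC is given, and a rationale is not evidence of correlation.** This stands. A reader might infer that the type I error is above 5% as a matter of fact. The documents do not support that: at ICC 0, including the case where the groups have no effect of any kind, the t-test keeps its level. The null hypothesis, however, is a zero mean difference, and good and poor groups can average to zero. Confidence intervals are too narrow whenever the ICC is positive, including when the effect is real.

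**The inflation may be small.** This stands in part. At ICC 0.02 or less it is about one percentage point or below, and Step 5 shows how drop-out or site-level correlation reduces it. Nothing in the article shows that the ICC is that small. Conductor pairs who run several groups could add correlation.

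**The article also counts control groups.** A reader might infer clustering in both arms and apply a full design effect. Under RCT design, controls join a group only after the last assessment, so they are ungrouped at both outcome times. The calculation above clusters the active arm only.

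**A detailed analysis plan is promised before analysis.** It could add a group term, and it is not shown here. But the article does not leave the test open: it names one for the primary hypothesis and extends it to the other outcomes. The later plan would have to change a stated rule.

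**The correction threatens blinding.** This stands. Clusters in one arm and singletons in the other show which of A and B is active, and the Blinding section keeps researchers blind during analysis. The remedy must deal with this.

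**Conclusion.** The point holds in conditional form. The stated primary test, its fallback and the sample size all assume independence, and the active arm's group delivery makes that assumption doubtful. If outcomes correlate within writing groups, the type I error at a nominal 5% is about 5.4–5.5%, 5.8–6.1%, 7.1–7.7% and 9.2–10.4% at ICC 0.01, 0.02, 0.05 and 0.10. These figures rest on assumed ICCs, m = 8–10, clustering in the active arm only and full exposure to the groups. They are lower if many active participants leave the groups or if part of the correlation is site-level.

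A reader might also infer that 300 participants are too few. The documents do not show that. Before drop-out, 150 per arm keeps 90% power up to an ICC of about 0.03–0.04 by the normal approximation, or about 0.02–0.03 with Satterthwaite degrees of freedom. What fails is the unconditional statement of at least 90% power.

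**What to change.** Before analysis, and in the analysis plan still to be lodged:

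1. For all full-sample outcomes, replace the t-test with a partially nested linear mixed model: a random writing-group effect in the active arm only, each control as a singleton, and small-sample degrees of freedom (Satterthwaite or Kenward-Roger). Cluster-robust standard errors with a small-sample correction are an acceptable simpler alternative. The linear-model fallback needs the same treatment.
2. Carry writing group into the multiple imputation.
3. Report the estimated ICC for the primary outcome.
4. Restate the 90% power as conditional on a stated ICC.
5. Protect the blind: fix the model code in advance, have someone outside the blinded team run it, and return only A/B-coded results. The Blinding section currently gives the outside employee data extraction only, so this task must be added.

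Adjustment for baseline QPR or site, and arm-specific residual variances, are separate choices that this correction does not require.

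**Cost.** No extra participants are needed for the analysis change. Co-conductors already record attendance at each session, so group membership can be identified. The price is slightly wider intervals, a less favourable power statement and the outside analyst's time.

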**Methods:**

The RCT is an investigator-initiated, randomised, two-arm, assessor-blinded, multi-center, waiting-list superiority trial involving 300 participants (age > 18) from six psychiatric centers in regions Capital and Zealand in Denmark, randomised to receive either the creative writing intervention combined with standard treatment or standard treatment alone. Assessments will be conducted before and after the intervention and at six months post intervention. The primary outcome is personal recovery at the end of intervention measured with the questionnaire of the process of recovery. Secondary outcomes include other measures of personal recovery, self-efficacy, mentalising, and quality of life. The pilot RCT, integrated within the RCT, will focus on 70 of the participants aged 18–35 with schizophrenia spectrum disorders, evaluating exploratory measures related to perspective-taking, social cognition, cognitive function, psychosocial functioning, and symptom pressure.

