### Objectives

Objective 1 of this study is to determine if REWRITALIZE as supplement to standard mental healthcare is more effective than standard mental healthcare alone for promoting personal recovery, as measured by the Questionnaire for the process of recovery (QPR) immediately after the end of the intervention, in a sample of individuals with severe mental illness.Objective 2 is to investigate if REWRITALIZE as supplement to standard mental healthcare is more effective than standard mental healthcare alone in promoting mentalising, self-efficacy, functioning and quality of life, as measured at the end of the intervention, and in promoting personal recovery six months after the end of the intervention.Objective 3 is to explore REWRITALIZE as supplement to standard mental healthcare for advancing clinical recovery variables, specifically cognition and social cognition, and pilot-test if REWRITALIZE leads to symptom reduction and improve psychosocial function in a smaller sample of participants with schizophrenia spectrum disorders.

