### RCT design

The RCT is designed as an investigator-initiated, randomised, two-arm, assessor-blinded, multi-center, waiting list-controlled superiority trial. The allocation ratio to active and control condition is 1:1. The participants (*n* = 300) will be randomised to active condition (REWRITALIZE plus standard treatment) or waiting list control condition (standard treatment) (see Randomisation below). As it is a waiting list control group, the persons randomised to the control group will be invited to participate in a creative writing group after the last assessment (within one year). To ensure high methodological quality, the trial is designed and will be reported according to the SPIRIT 2013 Statement and the modified CONSORT 2017 criteria for non-pharmacological trials [15, 17]. Data will be collected at baseline, at the end of the intervention (approximately 4.5 months after baseline) and six months after the end of the intervention (approximately 10.5 months after baseline). A flow chart of the study is provided in Fig. 2.

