*SR* self-report questionnaire; *T* task; *CR* clincian-rated; *TBS* Thwarted belongingness scale; *WSAS* Work and Social Adjustment Scale; *SEPRS* Self-efficacy for personal recovery scale; *MANSA* Manchester Short Assessment of Quality of life; *MentS* Mentalization scale; *TAS* Toronto Alexithymia Scale; *SCIP-D* Screen for cognitive impairment in psychiatry; *TASIT 2A* The awareness of social inference test; *VISPT* Visual perspective-taking task; *PANSS-6* Positive and Negative Syndrome Scale; *GAF-F* Global Assessment of Functioning Scale

The additional explorative outcome measures of the pilot RCT are also shown in Table 3. These include measures of cognitive impairment, social cognition, balancing of other-perspective, psychosocial function, and symptom severity. The outcome measures will be compared between active and control group at 4.5 months, and between baseline and at 4.5 months to explore feasibility of the measures.

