### Assignment of interventions

After baseline data are obtained, the participants are randomly allocated to either the control (standard mental healthcare) or active group (REWRITALIZE + standard mental healthcare) with a 1:1 allocation using the randomisation module in REDCap (Research Electronic Data Capture) [41, 42]. The randomisation sequence will be generated by an external researcher at Copenhagen Research Centre for Mental Health (CORE) and uploaded to REDCap. The randomisation is stratified by sites. Varying block sizes, unknown to the research team, are used. To ensure concealment, the randomisation schedule is stored away from the research team and the block sizes are not disclosed. Participants randomised to the control group will be set on a waiting list and will be informed that they will be offered to participate in a creative writing group within one year of the randomisation.

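### The Data analyses section gives conflicting instructions for the five pilot outcomes: tested at 0.05 as exploratory measures, or only described; estimation would suit about 35 per arm better

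*Protocol article*

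**What the plan says.** All references are to the protocol article.

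- **Status of the outcomes.** Table 3 (Outcome measures) puts SCIP-D, TASIT 2A, VISPT, PANSS-6 and GAF-F, measured in the subsample, under the exploratory heading. The six full-sample questionnaires at 10.5 months are in the same table.
- **General testing rule.** Data analyses specifies an independent-samples t-test on follow-up values for QPR, then adds: "Secondary and exploratory measures will be tested by the same means". The 0.05 level is applied to every measure, and no pilot outcome is exempted. Baseline adjustment is used only if the arms are found to differ at baseline.
- **Pilot sentence.** The same section ends: "For the pilot study mean, standard deviation, within and between group differences on the outcome measures will be calculated". It names no test and no significance level.
- **Purpose of the comparisons.** Outcome measures says the pilot outcomes are compared between arms at 4.5 months and "between baseline and at 4.5 months to explore feasibility of the measures".
- **Aim and size.** Objective 3 includes the aim to "pilot-test if REWRITALIZE leads to symptom reduction and improve psychosocial function". Sample size and power calculations states: "For the pilot RCT no calculation of sample size has been made", and gives feasibility of the measures as the reason. The abstract says the pilot "will focus on 70 of the participants aged 18–35 with schizophrenia spectrum disorders".
- **Feasibility checks already planned.** Pilot RCT design lists means, variation, between-group and within-group differences, whether data are normally distributed, and whether ceiling effects appear.

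**The concern.** Someone writing the detailed analysis plan could follow either instruction in Data analyses and claim to comply with the protocol. One route yields five p-values judged at 0.05; the other yields summaries.

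The choice matters because the article says the pilot will inform the design of a full-scale trial. With this few participants, a non-significant result could be read as no effect and a chance result as a signal. Neither a significance test nor a mean difference between arms shows whether a measure is feasible in this population. Objective 3 adds to the difficulty by putting an effect question to a pilot whose size was justified by feasibility alone.

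Within-arm change needs similar care. SCIP-D, TASIT 2A and VISPT are tasks repeated after 4.5 months, and all participants receive OPUS or F-ACT care. Change within the active arm therefore mixes any treatment effect with practice, regression to the mean and change under usual care.

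**Working it through.** **Inputs from the article.** Pilot n = 70 (abstract; Pilot RCT design). "The allocation ratio to active and control condition is 1:1" (RCT design), so about 35 per arm. "The randomisation is stratified by sites" (Assignment of interventions), and no other factor is named, so an even split of the pilot subgroup is expected but not guaranteed. Five pilot outcomes (Table 3). Significance level 0.05, taken as two-sided.

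**Assumptions.** d = 0.4 is the QPR target effect and is borrowed for illustration. The article gives relevant differences for SCIP-D (3.6), GAF-F (4) and TASIT (4) but no SDs for them, so no pilot-specific d can be derived. Correlations between baseline and follow-up of 0.5 to 0.7 are assumed.

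**1. The plan's own figure.** For QPR, a difference of 4 with SD 10 gives d = 0.4. The normal approximation gives n per arm = 2(1.960 + 1.282)² / 0.4² = 131.3, so 132 per arm (264). The exact t-test gives 132.3, so 133 per arm and 266 in total, with power 0.901. The stated 266 is reproduced.

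**2. Power of a t-test in the pilot (noncentral t).**

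| Per arm | Power, d = 0.2 | Power, d = 0.4 | d for 80% power | d for 90% power |
|---|---|---|---|---|
| 35 | 13% | 38% | 0.68 | 0.79 |
| 30 | 12% | 33% | 0.74 | 0.85 |
| 25 | 11% | 28% | 0.81 | 0.94 |

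The rows for 30 and 25 per arm show the effect of assumed losses.

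**3. False positives.** Five independent tests with no true effect: 1 − 0.95⁵ = 0.226. Positive correlation among the outcomes would lower this.

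**4. Precision if the pilot estimates instead of tests.** The 95% CI half-width for the between-arm difference, in SD units, is t(0.975; 68) × √(2/35) = 1.9955 × 0.2390 = 0.477. An observed difference would also need to exceed about 0.48 SD to reach significance.

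Adjusting for the baseline value multiplies the half-width by about √(1 − r²):

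- r = 0.5: 0.477 × 0.866 = 0.413
- r = 0.6: 0.477 × 0.800 = 0.382
- r = 0.7: 0.477 × 0.714 = 0.341

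The baseline values needed are already scheduled (Table 5).

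**5. Within-arm change, a conditional figure.** Suppose a paired t-test at 0.05 were run in one arm of 35, with no treatment effect and a drift shared by both arms. The SD of change is √(2(1 − r)). A drift of 0.2 SD at r = 0.5 would be significant with probability 0.21; a drift of 0.3 SD at r = 0.7, with probability 0.61. The article does not plan this test. The figures show only why such change should not be read as an effect.

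**The case against.** The strongest reply is that the pilot sentence is specific and the testing sentence is general, so the specific one governs and the pilot is descriptive. The reference to exploratory measures could then mean the six full-sample questionnaires at 10.5 months. This is a reasonable reading, but the text does not secure it: both sets sit in Table 3 under one heading, the 0.05 level is set for all measures, and no exception is written. The ambiguity stands.

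Three other parts of the defence hold, and each limits what a reader might infer.

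- **That the pilot cannot meet its feasibility aim at all.** The article does not support this. Means, SDs, normality and ceiling effects are planned and serve part of that aim. The mismatch concerns the tests and the mean comparisons. Completion proportions and correlation tables can be left to the analysis plan, so their absence is no fault.
- **That significance tests of within-arm change are planned, or that change in the active arm is offered as proof of effect.** No passage sets a test or a level for within-arm change, and none confines it to the active arm. Control-arm change is useful information on practice and drift.
- **That the pilot is wrongly sized.** The lack of a sample size calculation is stated openly and explained, and d = 0.4 was never set for a pilot outcome. Low power counts against testing these outcomes, not against recruiting 70 participants.

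Objective 3 is also hedged, since it speaks of exploring and pilot-testing. Its wording still asks whether the intervention produces an effect.

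**Conclusion.** The point holds as a conflict between two instructions for the same five outcomes, one of which does not suit the pilot's size or stated aim. If the testing route is followed, power is about 38% at the illustrative d = 0.4, only effects of about 0.68 SD or more are detected with 80% power, and the chance of at least one false positive is up to about 23% if the tests are independent. These figures assume about 35 per arm with complete data and two-sided tests; losses would reduce power.

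Estimation makes better use of the same data: a half-width of about 0.48 SD, or 0.41 to 0.34 SD with baseline adjustment if the correlation is 0.5 to 0.7. The change is worth making before analysis, but it concerns the pilot only. The primary QPR comparison and its sample size are unaffected.

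**What to change.** 1. In Data analyses, state that the five subsample outcomes are exempt from the 0.05 tests. For each, report the between-arm difference at 4.5 months adjusted for its baseline value, with a 95% CI and no claim of significance. Make this adjustment unconditional, not dependent on an observed baseline imbalance.
2. Keep within-arm change, shown for both arms, as a description of practice effects and drift. State that it is not evidence of effect.
3. Reword Objective 3 so that it speaks of estimating differences and assessing the measures. In Outcome measures, reword the clause that gives the comparisons a feasibility purpose.
4. Leave the planned SD, normality and ceiling summaries as they are.

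The cost is a few sentences and a small results table, using data already scheduled. The one real loss is that no p-values can be quoted for the pilot outcomes.
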